### 8.3.2. Efficacy endpoints

Perform the imaging evaluation  $16 \pm 1$  weeks after the start of treatment for evaluating the primary endpoint. Moreover, whether or not the imaging evaluation is performed by the 16th week, the frequency of when the imaging evaluation is performed is variable. When a complete response (CR) or partial response (PR) in the overall efficacy is seen for the first time, an additional imaging examination will be conducted in the 4th week thereafter for confirmation. The evaluation is performed according to "11.1. Efficacy evaluation."

During the protocol treatment period, it is desirable to conduct an assessment by contrast CT or

contrast MRI using the same modality and imaging conditions used in the pre-enrollment assessment.

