### **2.1.3. Standard treatment by disease stage and summary of prognosis, prognostic factors/predictors**

As solid tumors contain a variety of cancer types, the mention of standard treatment and prognosis by stage is omitted in individual cancer types. For solid tumors with metastases/recurrences, median survival is often around 1-3 years. Median survival is often less than one year, particularly in patients with solid tumors who have had metastases/recurrences and who have completed standard treatment. Although clinical stages and pathological classifications are used to determine the treatment plan, it is still difficult in many cases to predict the therapeutic effect. In recent years with the development of molecular-targeted therapeutic agents, treatment selection has come to be performed based on cancer genome abnormalities as an effect predictor. Tests for these genome abnormalities are often regarded as biomarkers (companion tests, complementary tests) involved in the selection of molecular target therapeutic agents.

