#### 8.5. Follow-up

From the time of the first patient enrollment in this study to when the study is completed, follow-ups are performed every 6 months for a period of 3 years to confirm patient survival (in case of death, confirm the date and cause of death), and to confirm any exacerbation (presence and date of any exacerbation, or the date no exacerbation was confirmed). Confirmations of outcome can be done by phone or letter.

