| Adverse Events                       |           |                       |                  | ◎*7                        |                                       |
| Follow-up                            |           |                       |                  |                            | ◎                                     |

◎: Required, ○: Optional

\*1: Any time before enrollment

\*2: Within 14 days before enrollment

\*3: Select modality according to cancer type

\*4: Within 28 days before enrollment

\*5: Within 28 days before the start of treatment (including the date treatment started)

\*6: Required 16±1 weeks after the start of treatment (otherwise as appropriate)

\*7: From the start of protocol treatment to 30 days after protocol treatment discontinuation or the date of subsequent treatment initiation, whichever comes first. (assess the events to 30 days after treatment discontinuation or the date of initiation of subsequent treatment, whichever comes first). If adverse events are considered to be related to protocol treatment or they are severe regardless of relation to protocol treatment, follow-up will be continued as long as possible until the adverse event is considered

resolved, resolved, or stable.

\*8: Within 14 days after treatment discontinuation date

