## 11. Efficacy assessments

When any treatment is registered in this study, the tumor response effect assessment will be done according to procedures in “The New Guidelines for the Response Evaluation Criteria In Solid Tumors (RECIST guidelines) revised version 1.1 (JCOG Japanese translation revised version 1.1)”(15).

Although the determination interval of overall efficacy is not determined, a comprehensive evaluation is always performed 16±1 weeks after the start of treatment. Furthermore, in this study, we do not collect the details of the efficacy assessments, but collect in the eCRF only the results of the best overall efficacy (11.1.10.) that were confirmed in each treatment.

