### 11.1.5. Tumor response evaluation

16±1 weeks after the start of treatment and at the time of treatment discontinuation, and regardless of whether or not treatment will be prolonged, an evaluation of the target lesions and non-target lesions is to be made according to "8.2. Tests and evaluations during the protocol treatment period" in the same manner as during enrollment, and the diameters of the target lesions and any disappearance or exacerbation of non-target lesions are to be recorded in the chart.

Even if the overall efficacy is determined to be "PD," the protocol treatment is not to be discontinued if it is determined that continuation of the protocol treatment is clinically appropriate, and to continue the protocol treatment even after the overall efficacy is determined as PD, the efficacy determination during this period should be performed according to the following.

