### 12.3.2. Analysis of efficacy secondary endpoints

Among the secondary endpoints, the efficacy endpoints are overall survival, progression-free survival, and disease control rate. The efficacy analysis set is the FAS for each drug cohort, and analysis is performed for each drug cohort at the time of main analysis or the subsequent primary endpoint analysis. Survival curves, median survival time, and annual survival rates are estimated for each survival time using the Kaplan-Meier method. The 95% confidence intervals (two-sided) are estimated using the Brookmeyer and Crowley method for the respective median survival times. The 95% confidence intervals (two-sided) are calculated using Greenwood's formula for interval estimation of the annual survival rates. An accurate method (Clopper and Pearson method) based on a binomial distribution is used for interval estimates for the disease control rate.

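### Imaging is fixed only at week 16±1, so the Kaplan-Meier median PFS depends on local scan timing and can be pulled to about 15–17 weeks for true medians of 6 to 12 weeks

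*Protocol*

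**What the plan says.** **Scan timing.** Section 11 sets no interval for judging overall efficacy, except that "a comprehensive evaluation is always performed 16±1 weeks after the start of treatment". Section 8.3.2 says of other imaging that "the frequency of when the imaging evaluation is performed is variable", and the footnote to the calendar in Section 8.6 agrees: "Required 16±1 weeks after the start of treatment (otherwise as appropriate". Two further scans are tied to events. Section 11.1.5 requires evaluation "16±1 weeks after the start of treatment and at the time of treatment discontinuation", and after a first CR or PR Section 8.3.2 adds that "an additional imaging examination will be conducted in the 4 th week thereafter for confirmation". For outcome tracking, Section 8.5 states that "follow-ups are performed every 6 months for a period of 3 years"; these contacts ask whether and when exacerbation occurred.

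**Dating of PFS.** Under Section 12.2.2, PFS starts at enrollment. Progression seen on imaging takes the date of the scan, clinical exacerbation takes the date of the clinical judgment, and death counts on its own date.

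**Analysis.** Section 12.3.2 applies to each drug cohort: "Survival curves, median survival time, and annual survival rates are estimated for each survival time using the Kaplan-Meier method". Medians get a Brookmeyer-Crowley interval.

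**Population.** Section 2.1.3 says of the expected prognosis: "Median survival is often less than one year, particularly in patients with solid tumors who have had metastases/recurrences".

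**The concern.** A Kaplan-Meier median treats each recorded date as the date of the event. Here an imaging progression is known only to lie between two scans, and the gap between them is a local choice. In a population with such a short prognosis, many progressions may fall before the single fixed scan. Those that no symptom, death or extra scan reveals are all dated to about week 16.

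Two things are at stake. Cohorts can differ in median PFS because their patients were scanned at different times. And the interval around the median can exclude the true value while appearing to be an ordinary 95% interval.

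The data may also be insufficient to repair this later. Section 11 says that detailed efficacy assessments are not collected and that the eCRF holds only the best overall efficacy. The protocol does not mention collecting the date of the last scan without progression, which an interval-censored analysis needs as its lower bound.

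**Working it through.** The protocol states no PFS median, assumption or PFS-based sample size, so there is no figure of its own to reproduce.

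**Inputs from the protocol.** Fixed scan at weeks 15–17 from treatment start (8.3.2, 8.6, 11); scan date as progression date (12.2.2); cohort size 50 (12.3.1, which counts patients with measurable lesions; the PFS set may be larger).

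**Assumptions.** Exponential progression times with true median m of 6 or 12 weeks, so F(t) = 1 − 2^(−t/m). The scan is uniform on weeks 15–17. A share q of progressions is dated when they occur, by any earlier route, independently of timing. The rest are dated at the week-16 scan or, if later, at the next 26-week contact. There is no censoring. The protocol gives no q, so the whole range is shown. Times run from treatment start.

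**Step 1: when the median falls in the scan window.** By week 15 the recorded event fraction is q × F(15). The median stays in the window if this is below 0.5 and F(17) is above 0.5.
- m = 6: F(15) = 0.823, F(17) = 0.860; critical q = 0.5 / 0.823 = 0.61.
- m = 12: F(15) = 0.580, F(17) = 0.625; critical q = 0.5 / 0.580 = 0.86.

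**Step 2: observed median, 4,000 cohorts of 50.**

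| q | true 6 weeks | true 12 weeks |
|---|---|---|
| 0 | 16.2 | 16.6 |
| 0.3 | 15.8 | 16.5 |
| 0.5 | 15.4 | 16.2 |
| 0.6 | 14.6 | 16.1 |
| 0.7 | 10.5 | 15.8 |
| 0.8 | 8.2 | 15.3 |
| 0.9 | 6.9 | 13.6 |
| 1.0 | 5.8 | 11.7 |

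Up to about q = 0.5 the two truths can hardly be told apart; from about 0.7 they separate.

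**Step 3: effect of scan timing alone.** With q = 0 and a true median of 6 weeks, the observed median is 16.2 weeks with scanning only at week 16, and 8.0 weeks if the sites happen to scan every 8 weeks. The same drug shows about twice the median.

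**Step 4: does the 95% interval contain the true median?** At the true median, half of the patients have progressed, so the recorded event fraction is q × 0.5 for any m below 15 weeks. With n = 50, order-statistic limits cover the truth if 18 to 32 events are recorded by then. Coverage is P(18 ≤ Bin(50, q/2) ≤ 32): about 0% at q = 0.3, 5.5% at 0.5, 21.8% at 0.6, 49.4% at 0.7, 76.3% at 0.8, 92.1% at 0.9 and 96.7% at 1.0. The simple Brookmeyer-Crowley rule with Greenwood variance accepts 19 to 31 events, which gives slightly less: 2.9%, 14.1% and 37.8% at q = 0.5, 0.6 and 0.7.

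**Step 5: proportion progression-free at 17 weeks.** The true value is 1 − F(17). In the worst case, q = 0 with the scan at week 16, the observed value is 1 − F(16).
- m = 6: 14.0% true, 15.7% observed; difference 1.7 points.
- m = 12: 37.5% true, 39.7% observed; difference 2.2 points.

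Larger q shrinks the difference.

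**The case against.** **Events can be dated before week 16.** Section 12.2.2 counts clinical exacerbation on the day it is judged, even without RECIST progression, and counts death on its own date. Section 6.2.2 makes clinical deterioration a reason to stop treatment, which brings a discontinuation scan, and optional scans are allowed. This stands. A reader might infer that the median will read 16 weeks whatever the truth; the documents do not support that, because it depends on the unstated share q. These routes have limits, however. Sections 6.2.2 and 11.1.5 allow treatment to continue after imaging progression, so the discontinuation scan need not fall near it. Section 12.2.2 dates a suspected progression to the later confirming scan. Entry requires ECOG 0 or 1, so early progression may be silent.

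**The interval is not always too narrow.** This also stands. A further simulation under the same kind of assumptions put the interval width at about 0.6–1.6 weeks for true medians of 6–10 weeks with few early detections. For a true median of 6 weeks it was 4.2 weeks with half dated early (4.5 with exact dating) and 7.4–8.4 weeks with 60–80% dated early. Misplacement is the more general fault.

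**PFS decides nothing here.** Sections 12.3.1 and 12.4 rest the efficacy judgment and the interim rules on the response rate. PFS has no threshold, test or planned comparison between cohorts. A reader might infer that the plan cannot show which drugs deserve development; the documents do not support that.

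**Follow-up dates.** Section 8.5 asks for the actual date of exacerbation, so the 26-week grid in the simulation misdates later events. This stands, but it does not create the pull to week 16, which comes from progressions before that scan.

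**A Turnbull analysis could be left to an SAP.** True of the method, but it cannot be run if the protocol's data collection omits the date it needs.

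**Conclusion.** The point holds in conditional form. The median PFS of Section 12.3.2 depends on local scan timing. For true medians of 6 to 12 weeks it can be pulled to about 15–17 weeks, provided that fewer than about 61% (true 6 weeks) to 86% (true 12 weeks) of progressions are dated earlier. The nominal 95% interval can then miss the true value: at q = 0.5 it covers it about 5% of the time.

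This rests on exponential times, early detection unrelated to timing, n = 50 and no censoring. Because PFS runs from enrollment, the pull would sit at about 16 weeks plus the gap between enrollment and treatment start, which the protocol does not state. Differences in scanning habits between cohorts are possible under the protocol but not shown by it.

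This is a cheap improvement to a descriptive secondary endpoint, not a threat to the trial's main conclusions.

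**What to change.** 1. In Section 12.3.2, add for each cohort the progression-free proportion at the end of the mandatory scan window, 17 weeks from treatment start, with a 95% CI. Name it as the PFS figure to use when comparing cohorts. State its time origin, since PFS otherwise runs from enrollment. Say how patients with no scan in the window are counted: the calendar lists that scan under the treatment period, so it is unclear whether it is due in those who stopped earlier.
2. Keep the Kaplan-Meier median, state that it depends on scan timing, and support it with an interval-censored (Turnbull) sensitivity analysis bounded by the last scan without progression and the first scan with it.
3. Add the date of the last scan without progression to the eCRF, so that item 2 is possible.

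No extra scans are needed. The cost is one more eCRF date, a little more analysis, and less weight on the conventional median PFS.

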### 11.1.10. Best Overall Response

The overall response is “good” in the order of CR > PR > SD > PD > NE, and the best overall response is determined according to the following criteria. When it corresponds to the definitions of multiple classifications, it is classified as the better one in the order of CR > PR > SD > PD > NE. However, when there are no target lesions at baseline, the best overall response does not use PR, and uses non-CR/non-PD instead of SD.

- **Complete Response (CR):**

When an overall response of CR is obtained two or more times continuously at intervals of 4 weeks (28 days) or more.

Furthermore, the day when the second overall response of CR is confirmed and the best overall effect of CR is determined is the day of confirmed CR.

- **Partial Response (PR):**

When an overall response of PR or better (CR or PR) is obtained two or more times continuously at intervals of 4 weeks (28 days) or more.

Furthermore, the day when the second overall response of PR is confirmed and the best overall effect of PR is determined is the day of confirmed PR.

- **Stable Disease (SD):**

In the case where neither CR nor PR is obtained as the best overall response, and there is at least one overall response of SD or better.

However, the shortest period of SD is 6 weeks from the start of protocol treatment.

- **Progressive Disease (PD):**

When the overall response is PD without corresponding to a best overall response of either CR, PR, or SD.

- **Not Evaluable (NE):**

When all of the overall responses are NE.

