## 12.2. Definition of the endpoints

### 12.2.1. Primary endpoint

The primary endpoint is the response rate based on the best overall effect up to 16±1 weeks after the start of treatment among patients with measurable lesions in the FAS for each drug cohort. Subjects who do not achieve CR/PR by 17 weeks after the start of treatment, and if CR or PR is confirmed for the first time thereafter, are not included in the primary endpoint numerator.

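### The confirmation scan (4th week after first response) and the rule for confirmed CR/PR (28 days or more apart) agree only on day 28, and no tolerance is stated

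*Protocol*

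**What the plan says.** **Schedule.** Section 8.3.2 asks for one more scan when CR or PR is first seen, placed in the 4th "week thereafter for confirmation". It sends the evaluation to section 11.1. The only imaging date it fixes during treatment is 16±1 weeks; otherwise "the frequency of when the imaging evaluation is performed is variable".

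**Definition.** Section 11.1.10 grants a best overall response of CR or PR only if the status is obtained "two or more times continuously at intervals of 4 weeks (28 days) or more". Failing that, a patient with at least one overall response of SD or better is classed as SD, subject to a six-week minimum from the start of treatment.

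**Use.** Section 12.2.1 builds on this: "The primary endpoint is the response rate based on the best overall effect up to 16±1 weeks after the start of treatment". It is computed separately for each drug cohort and only in those who have measurable disease.

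**Other imaging.** The study calendar (8.6) requires imaging at 16±1 weeks and at completion of treatment, and leaves the rest to judgment. It does not list the confirmation scan. Sections 8.4 and 11.1.5 also call for imaging when treatment is discontinued.

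**The concern.** The scan exists only to confirm a response, yet its scheduled window ends where the qualifying interval begins. A centre that follows 8.3.2 to the letter can produce a second CR or PR assessment that 11.1.10 does not accept. If no later scan supplies the interval, the patient counts as a non-responder for the primary endpoint.

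The result could also differ between centres. One may book the scan on day 24 and record PR because the scheduled scan was done; another may apply the 28-day rule and record SD. There is no central review of response (2.3.6), and the eCRF holds only the best overall result and not the individual assessments (section 11). The collected data would not reveal the difference, although lesion measurements remain in the patient chart (11.1.5).

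**Working it through.** **1. The stated interval.** 4 weeks × 7 days = 28 days, as 11.1.10 says.

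**2. Overlap of schedule and rule.** Count the days in the 8.3.2 window on which the interval from the first CR/PR scan is at least 28 days.

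| Reading of the 4th week | Interval (days) | Days that qualify |
|---|---|---|
| First scan is day 0, fourth seven-day block | 22–28 | 1 of 7 |
| First scan is day 1, fourth seven-day block | 21–27 | 0 of 7 |
| The 4-week time point | 28 | 1 of 1, no margin on the early side |
| The week that begins after four completed weeks | 28–34 | 7 of 7 |

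On the first reading, counting working days only gives 1 of 5, whichever weekday the first scan falls on.

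**3. Which responses a later scan can still confirm.** A second assessment qualifies at any time from day 28 after the first, provided CR or PR has persisted. For the 16±1-week scan to serve, the first response must come at least 28 days before it:

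- scan at week 15: 105 − 28 = day 77, so first response by week 11
- scan at week 16: 112 − 28 = day 84, so by week 12
- scan at week 17: 119 − 28 = day 91, so by week 13

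A response first seen after week 13 cannot be confirmed by that scan under any timing. It depends on the extra scan, an optional scan or a discontinuation scan that still shows CR or PR. An earlier response that ends before the next qualifying scan is exposed in the same way.

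**4. What one response is worth.** Section 12.3.1 uses a Beta(0.6, 1.4) prior and asks for a posterior probability above 95% that the response rate exceeds 60%. With x responders among n, the posterior is Beta(0.6 + x, 1.4 + n − x).

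- 37/50: Beta(37.6, 14.4), P(rate > 0.60) = 0.971, criterion met
- 36/50: Beta(36.6, 15.4), P(rate > 0.60) = 0.944, criterion not met

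This agrees with Table 12.4, which gives 37 as the minimum at n = 50. One response is 1/50 = 2 percentage points. The inefficacy boundary behaves in the same way. At n = 15, P(rate > 0.20) is 0.083 with one responder and 0.010 with none. At n = 26 it is 0.131 with three and 0.045 with two. Stopping is considered below 0.05.

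**The case against.** The strongest reply is that the days 22–28 reading is too literal. The text reads as a translation, and 8.3.2 itself uses the 16th week to mean the 16-week time point. Read alike, the 4th week is the 4-week time point, which 11.1.10 equates with 28 days, and a scan on that day qualifies. Section 8.3.2 also directs the evaluation to 11.1, where the 28-day rule stands. This is a fair reading and may well be the intended one. It does not remove the problem: a scan one day early still fails, no tolerance is given, and centres must book from the written words. Only the days 28–34 reading dissolves the conflict, and nothing in the protocol selects it.

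A second reply is that an early scan does not forfeit the response. That is correct, because any later assessment still in CR or PR and at least 28 days after the first will confirm it. A reader might infer that the week-16 scan is the only other required one, but imaging at discontinuation is required too, and optional scans are allowed. The discontinuation scan has no fixed date and may coincide with progression, so it is not a dependable substitute.

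A third reply is that for a response first seen at 16±1 weeks, confirmation falls after week 17 whether it comes on day 24 or day 28. Whether such a patient counts turns on the cutoff in 12.2.1, which is a separate matter.

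**Conclusion.** Sections 8.3.2 and 11.1.10 are not aligned. On the literal reading, and on the time-point reading, they agree only on day 28. The mismatch bears on the primary endpoint because confirmed best overall response feeds it. The definition in 11.1.10 is clear in itself; the schedule is what needs to be brought into line.

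The size of the effect cannot be estimated from the protocol, which says nothing about when centres book these scans, when responses appear or how long they last. Two stronger inferences are therefore unsupported:

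- That six of seven responses would be lost. The 1-of-7 count concerns calendar days for a single scan, on one reading. It is not a proportion of patients.
- That the wording changes a cohort's conclusion. The 37/50 and 36/50 contrast sits exactly on the decision boundary, where any single change of status would tip the result. It shows what one misclassified response can cost, not that one will occur.

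What stands is an avoidable route by which a late or short-lived response can be scored SD, and by which centres can score the same course differently. It merits correction on those grounds.

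**What to change.** In 8.3.2, state that the confirmation scan is done at least 28 days after the scan that first showed CR or PR, matching 11.1.10. Put the same wording in the study calendar, for example as an addition to the imaging footnote that now names only 16±1 weeks.

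The cost is one phrase and one footnote, passed through the protocol-change procedure in 13.9. The number of scans, the endpoint definition, the prior and the decision thresholds are unchanged.
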